## Abstract

**Background:**

Positive psychology interventions have been found to enhance well-being and decrease clinical symptomatology. However, it is still unknown how flourishing can also be increased. Although multicomponent interventions seem to be necessary for this purpose, different formats can be used. A cost-effective approach could be a positive psychology-based self-help book with tailored email support to reach large target groups and to prevent dropout.

**Objective:**

This study will evaluate the efficacy of a comprehensive multicomponent self-help intervention with or without email support on well-being and flourishing, and will seek to determine the working mechanisms underlying the intervention.

**Methods:**

In this 3-armed, parallel, randomized controlled trial, 396 participants with low or moderate levels of well-being and without clinical symptomatology will be randomly assigned to (1) a self-help book condition with weekly email support, (2) a self-help book condition without email support but with a weekly information email, or (3) a waiting list control condition. Online measurements will be assessed at baseline, at post-test (3 months after baseline), and at 6 and 12 months after baseline.

**Results:**

The primary outcomes are well-being and flourishing (ie, high levels of well-being). Secondary outcomes are the well-being components included in the intervention: positive emotion, use of strengths, optimism, self-compassion, resilience, and positive relations. Other measures include depressive and anxiety symptoms, personality traits, direct medical and non-medical costs, life-events, and client satisfaction.

**Conclusions:**

This study will add knowledge to the efficacy and cost-effectiveness of a multicomponent positive psychology intervention. We will also explore who can benefit most from this intervention. If the intervention is found to be effective, our results will be especially relevant for public mental health services, governments, and primary care.

**Trial Registration:**

The Netherlands Trial Register NTR4297; http://www.trialregister.nl/trialreg/admin/rctview.asp?TC=4297 (Archived by WebCite at http://webcitation.org/6Uwb5SUUM).

##  Introduction

### Background

Since the introduction of positive psychology in 1998 [1], the proportion of published studies on this topic has grown rapidly each year compared to the entire field of psychological research [2]. Researchers have argued that the study of positive psychology is more capacious than the field of psychopathology because its primary focus is not on dysfunction but on well-being and optimal functioning [3]. Recent evidence indicates that positive mental health and mental illness are related but different continua [4-6]. This so-called two-continua model implies that individuals can experience positive outcomes such as life-satisfaction, meaning, and personal growth when mentally ill, and that the absence of mental illness does not automatically imply high levels of positive mental health [7,8]. As a consequence, researchers have underscored the importance of enhancing positive mental health in addition to preventing and treating mental illness, in clinical populations as well as in the general population [3,9].

A central aim in positive psychology is to increase the amount of flourishing worldwide [1,10]. Flourishing is defined as the presence of high levels of the affective or “feeling good” dimension of well-being (ie, hedonic well-being) in combination with high levels of the psychological functioning or “living well” dimension of well-being (ie, eudaimonic well-being) [4,9,11]. Compared to “languishers” (ie, people at the lowest levels of hedonic and eudaimonic well-being) and individuals with depression, research has shown that flourishers experience the least emotional distress and psychosocial impairment, have hardly any lost work days, and are most likely to survive [4,8]. Keyes and colleagues [12] have found initial support for the hypothesis that an increase in well-being protects against the development of mental illness. More specifically, they found that the risk for having a mental disorder was equally lowest for individuals who were flourishing in 1995 and in 2005, and for individuals who were flourishing in 2005 but not in 1995 [12]. The same study also indicates that it is possible to enhance the amount of flourishing [12]. However, there seems to be significant room for improvement because epidemiological studies using the same operationalization of flourishing have found that there were only 17% flourishers in the United States [4], 20% flourishers in South Africa [13], and 37% flourishers in The Netherlands [14]. Some researchers theorize that even small improvements in the level of well-being in the general population could generate large preventive effects on the amount of psychopathology [9,15]. Yet, little is known about how the amount of flourishing can be increased. The present study will evaluate a theory- and research- based positive psychology intervention (PPI) on efficacy, specific working mechanisms, and cost-effectiveness for enhancing well-being and flourishing in the general population.

### Positive Psychology Interventions

A large number of theories have been used to develop interventions and exercises within the positive psychology movement, as can be found in the Key Competence Happiness Database [16]. Two meta-analyses have shown that PPIs significantly enhance well-being and alleviate depression in the short term, although effect sizes were relatively small [17,18]. These small effect sizes might be a result of the nature and intensity of the included interventions, which were mostly single-component interventions (ie, one or more individual exercises targeting one component of well-being). Examples are “the three good things exercise” or “savoring” targeting positive emotion, and “using one’s strengths in new ways” to increase flow. However, since well-being is a multifaceted construct [10,19] it might be more efficacious to promote well-being and flourishing with a multicomponent intervention that contains a variety of evidence-based individual exercises targeting 2 or more theoretically relevant hedonic and eudaimonic well-being components. For example, the well-being theory of Seligman [10] states that the components of positive emotion, engagement, relationships, meaning, and accomplishment (PERMA) are all necessary for flourishing. Also, multicomponent interventions are higher intensity, target more resources of well-being in an individual, and are often of longer duration than single-component interventions, which may increase their efficacy.

In the last decade, some multicomponent PPIs have been investigated, including different face-to-face interventions. Examples are (1) Positive Psychotherapy, a structured 14-session program developed for individual or group therapy in clinical settings based on Seligman’s well-being theory [10,20,21], (2) Well-being therapy, an individual psychotherapeutic strategy of 8-12 sessions that is based on Ryff’s model of psychological well-being [19] and therefore contains strategies and therapeutic techniques to influence the components self-acceptance, environmental mastery, positive relations with others, personal growth, autonomy, and purpose in life [22], and (3) the Working for Wellness Program, a structured 6-week group-based program for employees with a strong focus on strengths, flow, and social relationships [23]. The efficacy of these multicomponent PPIs on mental illness and positive mental health have been demonstrated in a wide variety of studies—including randomized controlled trials (RCTs)—although most of these studies used small samples [20,22,23]. However, the need for trained therapists in these intensive face-to-face PPIs is a disadvantage that may limit their feasibility, cost-effectiveness and dissemination.

Positive psychology exercises have the advantage of being relatively small and easy-to-implement in daily life, and are therefore well-suited for self-administered interventions. Recently, some Web-based multicomponent PPIs have been developed to increase the reach of PPIs. For example, Schueller and Parks [24] selected 6 exercises from the Positive Psychotherapy intervention (active-constructive responding, gratitude visit, life summary, three good things, savoring, and strengths) and randomly assigned participants to a 6-week program containing all 6 exercises, 4 of the exercises, or 2 of the exercises. The 2- and 4-exercise programs resulted in significantly larger effects on depressive symptomatology than the control group and the 6-exercise program, although participants in the latter program practiced the exercises on significantly more days than participants in the 2- or 4-exercise programs [24]. Another, more comprehensive intervention is Psyfit. This intervention contains 6 modules, each with 4 lessons, about goal setting, positive emotion, positive relations, mindfulness, optimism, and mastery [25]. An RCT showed significant but small effects on well-being and depressive symptomatology, although most participants completed less than 4 lessons of 1 or more modules [25]. While these and other Web-based multicomponent PPIs have shown that they can reach many individuals, their cost-efficacy seem to be limited by low adherence rates [24-27], which could be due to the lack of human contact and coaching [27,28].

### Self-Help Book With Email Support

Another, possibly cost-effective approach could be to intertwine the advantages of the aforementioned formats by using an accessible self-help book in combination with email support to reach and stimulate large groups of individuals at minimal costs. Meta-analyses have shown that the use of self-help books—also called bibliotherapy—with or without support are effective in the treatment of depression [29,30] and the treatment of alcohol problems [31]. Also, research on guided self-help in the form of email support in combination with face-to-face therapy or online therapy has shown promising results [32,33]. Besides, there are some indications that tailored email support is more effective than no support or automated email support [32,34]. More important, promising findings have been found for the use of positive psychology-based self-help books without any support [35-37] or with email support [38]. For example, Parks and Szanto [37] compared a PPI group of students who received the book “The How of Happiness” [39] to a group of students who received a cognitive behavioral self-help book to cope with depression and a control group. Results showed that both intervention groups were equally effective in reducing depressive symptoms at post-test compared to the control group, and that significant increases in life-satisfaction were found only for the PPI compared to the control condition at the 6-month follow-up. Another study used a multicomponent self-help book based on acceptance and commitment therapy in a sample with mild to moderate depressive symptomatology [38]. One intervention group received the book with extensive and tailored email support on progress and process, while another group received the book with minimal email support on progress. Results revealed significant increases in well-being and mindfulness and significant decreases in depressive, anxiety, and fatigue symptomatology for both intervention groups at 3-months follow-up compared to a waiting list control group [38]. In this study, we will use a version of the extensive email support similar to that used in the latter study [38]. That is, participants will be guided through the self-help book by tailored email feedback from trained counselors, but we will compare it to receiving an information email instead of minimal email support.

### This Study

This study will examine a comprehensive multicomponent positive psychology-based self-help book with email support. The self-help book is entitled, “This is your life” (TL) [40] and targets 6 key components in positive psychology: positive emotion, use of strengths, optimism, self-compassion, resilience, and positive relations. We will compare a condition wherein participants receive the book with weekly asynchronous and tailored email support (TL-E) to a condition wherein participants receive the book with a weekly email with information (TL-I). Both groups will be compared to a waiting list control condition (WL). Our research aim is to evaluate the efficacy of the multicomponent self-help book with or without email support in terms of well-being and flourishing in an RCT (NTR4297) and to evaluate which of the included well-being components in the self-help book contribute to its efficacy. We expect that TL-E will be equivalent or superior to TL-I and superior to WL at post-test and 6 months follow-up, and that the effects will be sustained at 12 months follow-up.

This study will add to current knowledge in 3 ways. First, it will be conducted in a sample with low or moderate levels of well-being without moderate or severe clinical symptomatology, which is a potential “happiness-seekers” group [41] that has not previously been studied in PPIs [17,18,27]. Second, this study will gain insight into the working mechanisms underlying the intervention by evaluating which of the included well-being components in the self-help book (ie, positive emotion, use of strengths, optimism, self-compassion, resilience, and positive relations) contribute to its efficacy and by examining individual differences in demographic characteristics, number of life events, personality traits, and adherence rates. Third, this study will examine if the innovative format used in this study (ie, self-help book with relatively inexpensive email support) is a cost-effective approach for enhancing well-being and flourishing compared to a waiting list control group, since little is known about the cost-effectiveness of PPIs [26].

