### Sample Size

Well-being is the primary outcome used for the power calculation. We expect to detect a significant effect on well-being between the experimental groups TL-E and TL-I compared to the WL group. Based on recent meta-analyses [17,18] and a previous comparable study [38], we expect to find a standardized effect size on well-being of 0.40 or larger. The targeted sample size is 99 participants per group (297 in total) to provide a statistical power of (1 - *β*) = 80% and a 5% significance level (two-tailed). To allow a study dropout rate of 25%, we need 132 participants in each condition and 396 participants in total for the trial.

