### Statistical Analyses

The Consolidated Standards of Reporting Trials (CONSORT) statement [91] will be used to report the results. Independent *t* tests and Chi-square statistics (X^2^) will be used to examine baseline differences between the study groups. Non-significant socio-demographic differences at baseline will indicate successful randomization. Internal consistency of the constructs will be determined using Cronbach’s alpha. To examine the efficacy of the intervention, intention-to-treat analyses will be conducted by including all participants in the analyses who have been randomized. The Expectation Maximization (EM) method will be used to impute all missing data on the continuous measures of T1, T2 and T3. This method imputes the data by maximum likelihood estimation using the observed data in an iterative process [92]. The intention-to-treat analysis will be compared with a completers-only analysis.

To examine significant differences between the 3 groups, we will perform repeated measures ANOVA in a 3 (group) x 3 (time) design with well-being (MHC-SF and FS) as the primary dependent variable and positive/negative emotions (mDES), the use of strengths (SUS), optimism (LOT-R), self-compassion (SCS-SF), resilience (BRS), and positive relations with others (SPR) as the secondary dependent variables. Significant time x group interactions will be tested with Tukey’ post hoc tests. Within-group effects (Cohen’s *d*) will be calculated by subtracting the mean post-test or follow-up score from the mean baseline score and dividing the difference by the pooled standard deviation. Between-group effects (Cohen’s *d*) will be calculated by subtracting the mean post-test or follow-up score of the experimental group from the mean post-test or follow-up score of the control group, and dividing the difference by the pooled standard deviation [93]. These effect sizes are used to gain insight into the relevance of the significant effects. To examine changes in the amount of flourishers, languishers, and moderately mentally healthy (MHC-SF), descriptive statistics will be used. Changes in categories will be tested with X^2^-statistics.

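### The hypothesis, the sample size and the analysis do not share one primary comparison, no arm contrast or time point is ranked first, and the 80% power belongs to a test that the plan does not perform

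*Protocol article*

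**What the plan says.** All references are to the protocol article.

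- **This Study (comparisons planned).** The aim covers the book with or without email support, and of the two book arms it says: "Both groups will be compared to a waiting list control condition (WL").
- **This Study (results predicted).** "We expect that TL-E will be equivalent or superior to TL-I and superior to WL at post-test and 6 months follow-up". This covers TL-E v TL-I and TL-E v WL. TL-I v WL has no prediction.
- **Sample Size.** "We expect to detect a significant effect on well-being between the experimental groups TL-E and TL-I compared to the WL group". The effect is given as "we expect to find a standardized effect size on well-being of 0.40 or larger", with power and alpha of "80% and a 5% significance level (two-tailed"). The result is "The targeted sample size is 99 participants per group (297 in total"), and then "To allow a study dropout rate of 25%, we need 132 participants in each condition and 396 participants in total for the trial". No time point is named, and TL-E v TL-I does not appear.
- **Statistical Analyses.** "To examine significant differences between the 3 groups, we will perform repeated measures ANOVA in a 3 (group) x 3 (time) design", run on both MHC-SF and FS. A significant interaction is followed by Tukey tests. These cover all three pairs, and no time point is named.

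**The concern.** The comparison that is predicted, the one that is sized and the one that is tested should be the same. Here the three sections give three sets: {TL-E v TL-I, TL-E v WL}, {TL-E v WL, TL-I v WL}, and all three pairs. WL participants receive the book only after the 6-month assessment, so post-test (T1) and 6 months (T2) are both controlled time points, and neither is put first.

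Two things are at stake. First, two book arms and two time points give four WL contrasts, each of which could be reported as the main result. A trial that needs any one of them is much easier to win than a trial that needs all of them, and the text does not choose. Second, the stated power has to belong to the test that decides the trial.

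**Working it through.** **1. The plan's own figure.** Inputs from Sample Size: d = 0.40, SD 1, two-sided alpha 0.05, power 0.80.

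n per group = 2 × [(1.960 + 0.842) / 0.40]² = 98.1, rounded up to 99. Allowing for dropout, 99 / 0.75 = 132, and 3 × 132 = 396. The exact power of a two-group t test with 99 per group (noncentrality 0.40 × √(99/2) = 2.814, critical value 1.972) is 80.0%. The figures reproduce, for one unadjusted two-group test at one time point.

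**2. The same contrast under the planned Tukey test.** The critical value for three groups with 294 degrees of freedom is 2.356. Power is about Φ(2.814 − 2.356) = Φ(0.458) = 0.68 per WL contrast on scores. With all 132 per arm carrying full information, it is Φ(3.250 − 2.353) = Φ(0.897) = 0.815.

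**3. How often the WL contrasts disagree.** Assumptions that are not in the documents: d = 0.40 in both book arms at both T1 and T2, SD 1, one scale, and a common correlation r between time points of 0.4 to 0.8. Trials were simulated. "Split" means that some but not all of the four WL contrasts (two arms × T1, T2) are significant. The first four rows do not require the interaction to be significant first.

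| Test | n per arm | r | Any of four | All four | Split |
|---|---|---|---|---|---|
| Tukey, scores | 99 | 0.6 | 92% | 38% | 55% |
| Tukey, scores | 99 | 0.4 to 0.8 | – | – | 60% to 47% |
| Tukey, scores | 132 | 0.4 to 0.8 | – | – | 43% to 35% |
| Unadjusted t, scores | 99 | 0.6 | 97% | 55% | 42% |
| Tukey, scores, after a significant interaction | 99 | 0.3 to 0.8 | – | – | 43% to 51% |
| Tukey, scores, after a significant interaction | 132 | 0.3 to 0.8 | – | – | 34% to 39% |

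**4. Narrower readings, 99 per arm, scores, interaction not required.**
- One time point fixed: exactly one of TL-E v WL and TL-I v WL is significant in 22% (unadjusted) or 30% (Tukey). Both are significant in 69% or 53%.
- TL-E v WL only, at T1 and T2: the two times disagree in 10% to 26% (unadjusted) or 13% to 36% (Tukey), for r from 0.9 down to 0.3.

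**5. If the post hoc tests use change from baseline.** The article does not say whether they compare scores or changes. With Tukey, 99 per arm and the same r for baseline, the split rate is 63% at r = 0.4, 46% at 0.6, 27% at 0.7 and 6% at 0.8.

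**6. TL-E v TL-I.** If both arms have the planned effect, this contrast favours TL-E significantly in about 1% (Tukey) to 2.5% (unadjusted) of trials. The word equivalent in the hypothesis has no margin.

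**The case against.** A reader might infer that the three sections contradict one another on which contrast decides the trial. The text does not support that. This Study says that both book groups will be compared with WL and covers the book with and without support, so all three pairs are planned there, and Tukey tests cover the same three. Sizing on two of the three is ordinary practice. What is left is a missing prediction for TL-I v WL and the absence of any ranking.

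A reader might also infer that no time point is named anywhere, or that half of all trials would end in a split. The hypothesis does name post-test and 6 months, and can be read as requiring both. It does not say so, and the other two sections name neither. One half is only a mid-range value. It needs four contrasts to be counted, 99 per arm and a moderate correlation. It falls with 132 per arm, which is the number the intention-to-treat analysis includes, although imputed cases carry less information. It can also fall far lower if baseline is used and is strongly correlated with follow-up.

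It is fair to add that a testing order can be left to a statistical analysis plan, and that the interaction test followed by Tukey gives some control across arms. Neither answers the point. The article itself fixes a hypothesis, a power basis and an analysis, and these do not line up. Tukey also does not choose between T1 and T2.

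**Conclusion.** The point holds as a mismatch and a missing ranking. The sample-size arithmetic is correct, but the 80% describes a single unadjusted two-group test. The planned Tukey comparison on scores has about 68% power per WL contrast with 99 per arm.

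If both book arms have d = 0.40 at T1 and T2, the four WL contrasts disagree in roughly 35% to 60% of trials. That range is for Tukey on scores, an assumed correlation of 0.4 to 0.8 and 99 to 132 per arm. It is lower if baseline enters the comparison and is strongly correlated. With one time point fixed and 99 per arm, the two WL contrasts still disagree in about 22% to 30%. No stated rule says how such a result would be read, so the arm and time point could be selected afterwards. This should be corrected. It does not make the design unsound.

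**What to change.** Before the data are seen:

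1. Name one primary contrast, one time point and one well-being scale, and use them in This Study, Sample Size and Statistical Analyses. An example is TL-E v WL on MHC-SF at T1, at two-sided 0.05. Another choice would serve equally well if it is made in advance. The scale must be named because MHC-SF and FS are both primary at present.
2. Test the remaining WL contrasts in a stated fixed order, each at 0.05, stopping at the first non-significant result. Alternatively, make the two WL contrasts co-primary with adjusted alpha and restate the power.
3. State that the omnibus ANOVA and Tukey tests are then supportive. Without this, the 99 per group still does not refer to the deciding test.
4. Report TL-E v TL-I as an estimate with a 95% confidence interval, and drop the word equivalent unless a margin is set.

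**Cost.** The fixed order needs wording in three sections and no more participants. Contrasts later in the order cannot be claimed as confirmatory if an earlier one fails. The co-primary route costs power or numbers. With Bonferroni at 0.025 each, 99 per arm gives about Φ(2.814 − 2.241) = 72% per contrast. Keeping 80% needs 2 × [(2.241 + 0.842) / 0.40]² = 118.8, so 119 per arm, or 119 / 0.75 = 159 randomised per arm.
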